**Aims:**

This study aims to explore intensive care nurses' perceptions of the applicability of currently used nursing models and theories and to develop a new Zambian critical care nursing framework based on the principles of Ubuntu.

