## Aims

2

The interlinked aims of this study are to explore the knowledge and understanding critical care nurses have of the current nursing models officially, identifying positives, challenges and constraints. These will then be used to underpin the conceptualisation and development of a new context‐specific framework for critical care nursing based on the identified African philosophy of Ubuntu, and of direct applicability in Zambia.

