### Data Analysis

3.3

The retrospective review of nursing care plans will use the extraction framework as indicated in Table 1. Data will be collected and transferred into a MS Excel spreadsheet. Data will be numerical: for example, how many times a NANDA‐I diagnosis is used and how many times the ADLs are included. This approach was seen as a practical measure to assess actual usage of the current recommended models. Descriptive statistics will be used to determine patterns and trends [26]. Where possible, tests for significant difference such as chi‐squared will be used to determine significant differences, as the majority of the data will be nominal or ordinal [27]. For open‐ended questions, data will be coded and analysed using framework analysis processes [23].

Focus groups will be conducted with different nursing groups as outlined above. A maximum of six participants will be invited to each focus group, and MS Teams will be used to record the discussions, as this will facilitate immediate transcribing. Focus groups will be scheduled during the handover period to allow participants to attend, to reduce the impact on patient care and will be conducted in an office away from the clinical area, but within the hospital. Following the focus group, the MS Teams transcript will be downloaded and saved as an MS Word document. Framework analysis will then be used to analyse the interviews [23]. Only the research team will have access to the raw data sets. All data will be analysed by the research team, including a Zambian Researcher who will provide context validation for the coding process. Framework analysis is considered more transparent and robust than thematic analysis [28]. Open coding of the transcript entails constant comparisons supporting the emergence of initial categories. A more focussed second in‐depth analysis includes reviewing data for context [28, 29]. This iterative analysis facilitates interconnectedness [28, 30], facilitating analysis, both within and across data sets [29]. This will include searching for phrases that fit with the Ubuntu philosophical discussion.

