### Development of the Framework

4.1

The overall approach framework used in this study is such that all activities entail interaction with key stakeholders. The statistical analysis will indicate the extent to which the current models are used in nursing documentation. This will also identify the differences to Ubuntu philosophy [35, 36]. Integration of the quantitative data sets and the findings from the focus groups will be used to facilitate review of the current documentation, and how well these fit with the care given. They will be used to support the development of the proposed new framework to provide excellence in critical care professional practice [39, 40]. As Mugumbate and Chereni [19] suggest, using Ubuntu principles will change the approach to care, to one in which the interconnectedness, shared responsibility and progression, link the care with service providers and the care given. Therefore, documentation needs to be couched in language that reflects the shared vested interest in the individual within the group [41]. Key issues will be extracted from the integrated data sets and essential points for the new framework developed with stakeholders [36].

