## Limitations

5

It is accepted that this is a small‐scale study in a single‐centre study; however, as the leading ICU in the country, findings may still be generalisable. In addition, this is one of the first studies in this area of critical care nursing practice and will provide insight into the current use of nursing models and provide an opportunity to develop an initial Ubuntu‐based framework for critical care nurses, which could then be scaled up. A review of the model by stakeholders will support refining and adjustments to the overall structure of the framework, an approach successfully used in a previous study to review and update specific documentation [42]. To reduce bias, researcher triangulation will be used during the data collection and analysis. All researchers will maintain a reflexive journal; this will be used throughout to check that research positionality does not adversely affect analysis. As this study involves an international research team, debriefing and supervision is an integral component as it will challenge assumptions and support the clarity needed to develop the new framework. Data processing will also be audited; this will be carried out by an independent researcher to further minimise bias.

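### The only content-directed search stated for the focus-group transcripts is for phrases that fit Ubuntu; no search is stated for phrases that conflict with it or favour the current models

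*Protocol article*

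**What the plan says.** Section 3.3 (Data Analysis) describes how the transcripts will be handled. The first step is inductive: "Open coding of the transcript entails constant comparisons supporting the emergence of initial categories". The second goes deeper: "A more focussed second in‐depth analysis includes reviewing data for context". The text calls this an iterative process that works within and across data sets, and ends with one named target: "This will include searching for phrases that fit with the Ubuntu philosophical discussion".

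Two other places set the context:

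- The Abstract (Aims) fixes the philosophy before any data are collected. The study sets out "to develop a new Zambian critical care nursing framework based on the principles of Ubuntu".
- Section 2 (Aims) commits to a two-sided enquiry into the models now in use, "identifying positives, challenges and constraints".

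Section 4.1 (Development of the Framework) then says that key issues will be drawn from the integrated data and turned, with stakeholders, into the essential points of the new framework.

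**The concern.** When a coding plan names one thing to look for, analysts look for it harder than for anything else. Here the named target is text agreeing with a philosophy that has already been chosen. Nurses may say that some element of Ubuntu does not suit ventilated patients, or that part of ADL or NANDA-I works well. Such statements depend on open coding alone to be noticed, while agreeing statements get open coding and a dedicated search.

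What is at stake is the content of the framework. Section 1 (Background) accepts that Ubuntu was not designed for critical care, and section 6 (Implications for Practice) says it has not yet been applied to critical care nursing. Where it fits intensive care poorly is therefore an open question. The focus groups are the natural place to find out before the framework is piloted. A study that builds on Ubuntu without testing it still needs the non-fitting material, to know what to adapt.

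**Working it through.** No arithmetic applies: the point concerns a qualitative coding rule and depends on no sample size, rate or error level. The check sets the relevant texts side by side.

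1. **Which transcript steps name content to look for?** Open coding names none, since categories are to emerge. The second review names context, which is a way of reading and favours no view. The Ubuntu search is the only step that specifies content, and it specifies agreement.

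2. **Is a counterpart stated in section 3.3?** No. Nothing there directs a search for statements that conflict with Ubuntu, fall outside it, or favour ADL or NANDA-I.

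3. **Is a counterpart stated elsewhere?** The nearest text is in section 4.1: "This will also identify the differences to Ubuntu philosophy". It follows directly on the sentence about the statistical analysis of nursing documentation. It therefore concerns how recorded care relates to Ubuntu, and does not cover nurses' dissent in the focus groups.

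4. **How does this compare with the Aims?** Section 2 asks for positives as well as challenges and constraints of the current models. Section 3.3 gives Ubuntu a directed search and gives the positives of the current models none. The two texts do not contradict each other, because open coding can pick up those positives. The directed effort, however, does not match the two-sided aim.

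5. **Is the starting position neutral?** No. Ubuntu is written into the aim. In Box 1, the row on use in critical care lists drawbacks for ADL and NANDA-I and none for Ubuntu. This makes the direction of the search matter more.

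6. **Do the safeguards close the gap?** Section 5 (Limitations) says: "To reduce bias, researcher triangulation will be used during the data collection and analysis". It adds reflexive journals, debriefing and supervision, stakeholder review, and an independent audit of data processing. Section 3.3 adds context validation of the coding by a Zambian researcher. These control who analyses and how carefully. None is stated to require a search for contrary statements or a report of them. Several analysts applying the same one-directional search can agree with each other and share its tilt.

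**The case against.** The strongest reply has four parts.

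**The search is one component.** The sentence says the analysis will include it, and open coding with constant comparison comes first, without an Ubuntu filter. This stands. A reader might infer that the analysis looks for nothing but Ubuntu, or that contrary text cannot be retrieved at all. The text supports neither reading.

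**Ubuntu is a declared premise.** The study sets out to build on it, and nothing says that the search output will be counted or used as evidence for it. In such a study, locating text relevant to the chosen lens is an ordinary deductive step. This also stands. A reader might infer that the study will confirm Ubuntu regardless of what nurses say, or that it fails as a test of Ubuntu. The first goes beyond the text, and the second faults the study for something it does not claim to do.

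**The safeguards are broader than triangulation and journals.** True, and supervision is meant to challenge assumptions. They reduce the risk, but they do not make a one-directional search two-sided.

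**The article condenses a fuller protocol.** Negative-case procedures and charting rules are often left to that document or to a coding manual, so their absence alone would be no finding. This limits the point but does not remove it, because the point rests on a rule that the article does state, and that rule is asymmetric as written.

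**Conclusion.** The point holds as a moderate one that should be corrected. The single content-directed search stated for the transcripts favours the philosophy chosen beforehand, and no counterpart is stated. The consequence is a risk of confirmation bias when key issues are extracted for the framework. It is not a demonstrated bias.

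Its size cannot be given as a number. It depends on how much contrary material the focus groups produce and how much of it open coding carries forward, and the article informs neither.

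The verdict assumes that the sentence in section 3.3 describes what the analysts will do, and that the full protocol, which is not shown, does not already pair it with a search for negative cases. If it does, the remedy reduces to saying so in the article.

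**What to change.** Amend the closing sentence of the focus-group paragraph in section 3.3 before the transcripts are coded, so that it states the following:

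- After open coding, each relevant segment is indexed as fitting, neutral to, or conflicting with Ubuntu.
- Segments about ADL and NANDA-I are indexed in the same way as positives or constraints of those models, in line with section 2.
- Non-fitting (negative) cases are charted in the framework matrix and reported alongside the fitting ones, so that both are in view when key issues are extracted under section 4.1.

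The existing open coding, context review and safeguards stay as they are. The cost is a few extra codes in the same matrix and modest analysis time. No new data, participants or focus groups are needed.

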### Ethics and Research Approvals

3.4

To promote equity and in accordance with Zambian requirements, ethics approval to complete this study was obtained from the University of Zambia Biomedical Research Ethics Committee (Ref.: UNZA‐7130/2025), and the study registered with the National Health Research Authority (Ref.: NHRA‐2723/22/09/2025). Approval to conduct this study has been granted by the hospital management team and the Senior Medical Superintendent. In addition, as this study involves an international team, full ethics approval was granted by the Birmingham City University Ethics Committee (Ref.: 15192). There is a risk that poor practice may be identified during the study, for example, poor documentation and incorrect care planning. However, it is accepted that participant confidentiality and data protection are crucial; therefore, any concerns will be addressed in a sensitive manner to avoid demoralising staff and a training package will be delivered to all staff. In addition, good practice identified during the study will be highlighted and shared. Outcomes will be included as part of the dissemination. In addition, all participants are registered nurses who are required to complete ongoing professional development/continuing professional development (CPD) as part of their annual re‐registration with the NMCZ [31]. Therefore, the dissemination/training event will contribute to nurses' annual revalidation requirements.

## Discussion

4

The urgent need to develop a context‐specific framework for critical care nursing in Zambia has been recognised and accepted by stakeholders and critical care nurses [8]. A key argument in this is that the HIC models of nursing are based on differing societal values, infrastructures and finances [12, 32, 33]. Adopting a framework based on Ubuntu recognises that caring, an essential component of nursing, cannot be viewed in isolation. In the African context, it involves recognising all aspects of an individual's being, which includes immediate and extended family members, ancestors, the community (and village) they come from and their tribe [34]. Zambia is not alone in seeking to contextualise care; within the African context, there is an increasing move to utilise African philosophies, such as Ubuntu as potential nursing models. These take account of the individual, the community and society as a whole. Adopting Ubuntu in critical care accepts the argument that the interconnectedness and shared societal responsibility extend to education and through that to practice [35].

Mulaudzi and Gundo [35] developed an Ubuntu community model in nursing in selected provinces in South Africa that demonstrated the interconnectedness of all aspects of life on health. Similarly, Carter [8] developed a career structure and conceptual framework for critical care nurses in Zambia based on the philosophy of Ubuntu. This recognises the individual and collective role of nurses and families, revealing how this can improve holistic care, and through that patient outcomes. Therefore, this study has the potential to build upon previous work and develop a framework for critical care nursing practice that will be fit for purpose for the country in which it will be used. There needs to be a focus on re‐designing processes and procedures to include placing the patient within their cultural and social place, rather than solely focusing on tasks resulting from domain diagnoses. This in turn facilitates individualised person‐centred care with documentation focused on the totality of care and the inclusion of context‐specific care designed to maximise the possibility of re‐integration into family and the community [15]. This contributes towards futureproofing the acceptability and appropriateness of critical care nursing practice. It will also fit with the move away from traditional colonial care practise that is evident across the African continent [36]. This will enable Zambia's critical care nurses to move forwards with their peers and develop unique care that is tailored to the population, following their own cultural heritage and patterns. In addition, this approach will also provide sustainability, build research capacity and empower local nurse researchers so that they can become independent. It is also important to note that research generated by local researchers and their recommendations may have a better uptake among African policy makers than research produced internationally as it is culturally and context‐specific [37, 38].

### Development of the Framework

4.1

The overall approach framework used in this study is such that all activities entail interaction with key stakeholders. The statistical analysis will indicate the extent to which the current models are used in nursing documentation. This will also identify the differences to Ubuntu philosophy [35, 36]. Integration of the quantitative data sets and the findings from the focus groups will be used to facilitate review of the current documentation, and how well these fit with the care given. They will be used to support the development of the proposed new framework to provide excellence in critical care professional practice [39, 40]. As Mugumbate and Chereni [19] suggest, using Ubuntu principles will change the approach to care, to one in which the interconnectedness, shared responsibility and progression, link the care with service providers and the care given. Therefore, documentation needs to be couched in language that reflects the shared vested interest in the individual within the group [41]. Key issues will be extracted from the integrated data sets and essential points for the new framework developed with stakeholders [36].

## Limitations

5

It is accepted that this is a small‐scale study in a single‐centre study; however, as the leading ICU in the country, findings may still be generalisable. In addition, this is one of the first studies in this area of critical care nursing practice and will provide insight into the current use of nursing models and provide an opportunity to develop an initial Ubuntu‐based framework for critical care nurses, which could then be scaled up. A review of the model by stakeholders will support refining and adjustments to the overall structure of the framework, an approach successfully used in a previous study to review and update specific documentation [42]. To reduce bias, researcher triangulation will be used during the data collection and analysis. All researchers will maintain a reflexive journal; this will be used throughout to check that research positionality does not adversely affect analysis. As this study involves an international research team, debriefing and supervision is an integral component as it will challenge assumptions and support the clarity needed to develop the new framework. Data processing will also be audited; this will be carried out by an independent researcher to further minimise bias.

## Implications for Practice

6

Little has been published from low–middle‐income countries on context‐specific critical care nursing models and frameworks. However, as critical care nursing evolves and matures, it is important that context‐specific frameworks and models for practice are developed. Ubuntu has been identified as a possible context‐specific philosophy that can be translated for use in nursing care; however, it has not yet been applied to critical care nursing. Critical care in many low‐income countries is advancing, and this study is seen as a first step in the development of a context‐specific critical care nursing framework. Stakeholders (including the Ministry of Health and NMCZ) will play a key role in dissemination and implementation of the findings. They are keen to see processes developed that are culturally competent and will align practice to the needs of the population they serve. Also using participatory cooperative inquiry approach, future pilots of the new model will be led by stakeholders who have the research expertise to lead and guide such ventures.

## Conclusion

7

This protocol provides an overview of a study to develop a context‐specific critical care nursing framework using an African philosophy to underpin practice. It offers an opportunity for critical care nurses to be empowered to lead and develop their own specialist area of practice.

## Ethics Statement

This study has been approved by University of Zambia Biomedical Research Ethics Committee (Ref: UNZA‐7130/2025), Birmingham City University, UK (Ref: 15192), and registered with the National Health Research Authority (Ref: 272322/09/2025).

## Consent

The authors have nothing to report.

## Data Availability

The data that support the findings of this study are available from the corresponding author upon reasonable request.
